## Methods/design

### Aims

This paper presents the study protocol for a BCI to improve the health of low-SES residents living in Rotterdam. The main aim of the current study is to evaluate the efficacy of a theory-based multicomponent intervention for low-SES residents living in Rotterdam. We hypothesize that in comparison to those in the control condition, participants receiving the intervention will have lower stress levels, will smoke less and have improved financial and self-perceived health.

### Study design

BeHealthyR is a three-arm RCT with three points in time: baseline (T0), four weeks post-baseline (T1) and twelve weeks post-baseline (T2). Between February 2018 and July 2019, a total of 300 participants will be recruited and randomized either to a stress management program (SM), stress management with a buddy program (SM-B) or a control condition (CC).

### Study setting and population

In collaboration with the municipality of Rotterdam and mental health organizations (indigo Rijnmond and Avant Sanare), the present study will be conducted in community centres in Rotterdam. A total of 300 residents aged 18 years and above will be included if they perceive stress, smoke and have poor financial health. A list of study sites is available on request from [contact].

### Recruitment of study population

Previous research has indicated that a multipoint approach is suitable for recruiting individuals from low-SES as these individuals are difficult to reach out to and less likely to take part in research [21]. Therefore, in the current study, eligible participants will be recruited using a multipoint recruitment strategy which involves recruiting via: 1) information at community and welfare organizations; 2) contacts with active key-figures; 3) online sources (i.e Facebook page and Website), 4) personal phone contacts by Indigo Rijnmond; 5) advertisements in local newspapers; 6) flyers placed in the general public in Rotterdam (i.e. supermarkets); 7) community places (i.e mosques, churches, secondhand shops, daycare centres and food banks); and 8) snowball sampling techniques. Eligible participants who express an interest in participating in the study will be invited to attend an orientation session. During the orientation session, the research team (SS, AS, IB, WV and research assistants) will give presentations about the research study and provide potential participants with information pamphlets containing: 1) an information letter about the study; 2) a screening questionnaire (checking the eligibility criteria) and 3) an informed consent form (see Additional file 1). If a participant meets the eligibility criteria, he/she signs the informed consent and returns it to the research team. A flowchart of participants recruited for the study is shown in Fig. 3.

**Fig. 3 Fig3:**
[figure not shown]
Flowchart of participants. SM = stress management condition; SM-B = stress management + buddy condition; T0 = baseline; T1 = 4 weeks after baseline; T2 = 12 weeks after baseline

### Inclusion and exclusion criteria

Eligible participants are over 18 years of age, reside in Rotterdam, perceive stress, smoke and have poor financial health. All study participants must have adequate Dutch-language skills and provide written informed consent to take part in the study. Participants will be excluded from the study if they: 1) follow other stress management or smoking cessation courses; 2) receive help from debt services for their financial problems; or 3) have health problems which hamper their ability to take part in the study.

### Randomization and blinding

Once eligibility is checked and consent is gained, participants will be randomly allocated to three conditions in a 1:1:2 allocation ratio using computer generated random numbers. For practical and logistic reasons (i.e low number of participants per group session), randomization will be done on group level (i.e potential participants attending a specific training session at a community center will be randomized to the same intervention arm). To minimize the risk of bias, randomization will be done by the principal investigator (AS) Fig. 4 shows the randomization scheme of study participants.

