### Intervention and comparison groups

#### Intervention group with stress management course only (SM)

The SM program is an adaption of the existing course *Less Stress* developed by Trimbos institute [53] and has been tailored to meet the specific needs of low-SES participants. A core element of SM is its group-based format in which psycho-educative topics on stress responses and coping and motivation to stop smoking link up with cognitive and behavioral technique activities. The SM consists of four weekly sessions (1.5 h/session) and a follow-up session eight weeks later. The psycho-educative topics are discussed in the following order: introduction to stress, thinking habits, coping skills, setting boundaries, goal-setting and self-affirmation exercises, motivation to stop smoking and self-reflection. In session one, participants are offered general information on stress, the types of stress, stress signals and the effects of stress on health. After some theoretical background, participants learn the techniques of progressive relaxation and breathing exercises. Furthermore, BCT is utilized in the form of a 20- min goal-setting activity in which participants will be asked to set goals. This activity will be repeated once every month over the course of the study duration. In session two, BCT is utilized in the form of a 20-min self-affirmation activity carried out during the session. To increase self-affirmation, participants will be asked to write about their core values (i.e family, religion), why these values might be important to them and to rank these values in terms of their personal importance. The self-affirmation task is performed once over the course of the study period. Also, in session two, cognitive techniques (CT) are applied in which participants will be asked to identify, reframe and replace negative thinking habits with positive ones. In session three, participants will learn how to apply coping skills learned in previous sessions. In session four, participants will learn about healthier habits on how to reduce physical stress reaction and also rehearse the knowledge and techniques learned in previous sessions. Between sessions four and five, participants will be invited to a smoking cessation meeting during which professional smoking cessation counselors will provide information on strategies on how to stop smoking and maintain smoking abstinence. Participants will also receive self-help material and information on smoking cessation programs. Finally, in session five, participants will be asked to create their own Relapse Prevention Map (RPM). By creating a personalized RPM, participants will be able to plan ahead for high risk situations (i.e how to cope better with stress or how to resist smoking cravings).

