### Statistical analysis

#### Sample size calculations

Sample size calculations are based on the primary outcome measures (stress, smoking, and perceived health). To the best of our knowledge, no previous studies have evaluated a similar intervention in low-SES groups. Therefore, it is challenging to determine a prior the necessary sample size for multicomponent behavioral interventions. Previous studies that have evaluated similar components on other outcome measures recommend to aim for a sample size of 20-500 participants per intervention condition with an alpha error of 0.05 and a power of 0.80. to detect the expected effect. Assuming expected attrition of 10%, an initial sample of 300 participants are needed, thus 150 in each intervention condition. All power calculations are done using G*Power [76].

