### Data analysis

All statistical analyses will be performed using the Statistical Package for the Social Sciences (SPSS v21) software program. Baseline descriptive statistics will be conducted to describe the study sample using two-sided t-test for continuous variables (i.e. age at enrolment), chi-square tests or Fisher’s exact tests for categorical variables (i.e. gender, nationality, level of education). Logistic regression analysis will be performed for outcomes with two categories (i.e. good health vs bad health, high stress vs low stress, intention to quit vs no intention to quit). Multinomial regression analysis will be conducted for outcomes with more than two categories (i.e. improved, constant or deteriorating financial situation). Age, gender, and nationality will be treated as potential confounding variables. Missing data will be evaluated (depending on the amount and pattern of missingness) using different approaches. Sensitivity analyses will be done using imputation techniques for missing data to assess the robustness of the main analysis.

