## Discussion

This paper describes the protocol for an RCT designed to evaluate the effectiveness of a multicomponent theory-based intervention. It is hypothesized that after a successful implementation of the intervention, the intervention will lead to a reduction in stress, smoking, and improvement in financial and self-perceived health. Previous studies have raised concern about the lack of effective interventions for low-SES populations [16]. By conducting this study, we hope to fill these evidence gaps. This study has several strengths. A key strength is the originality of the study. To the best of our knowledge no previous studies have evaluated the effects of similar components used in the current study to reduce stress, smoking, improve financial and self-perceived health in low-SES groups. Another strength of the current study is that it addresses the efficacy of the intervention by using an RCT design. Random allocation of study participants to the different conditions excludes all possible bias (selection and allocation bias). Another strength is the follow-up period of 12 weeks which allows insight into short-term effects. Finally, by incorporating a process evaluation and a cost-effectiveness analysis, we can gain insight into the facilitators/barriers of the implementation and whether the intervention can be scaled up in different settings, respectively. Finally, the intervention will be conducted in a real-life setting, which will make to generalize the effects to similar low-SES groups in the Netherlands.

Some limitations should be considered. First nonadherence and drop-outs could occur. Previous studies have indicated that low-SES individuals drop out quickly from preventive interventions [17]. In the current study, we have taken this into account. In order to prevent high dropout and maintain participation retention, we have used nudges, to reward and motivate the study participants to stay engaged in the intervention. In addition, the use of buddies for the financial support can be a risk for professionalism of our interventions because these buddies are unexperienced. However, the risk is minimal because these buddies are selected carefully and receive extensive training on financial debts by trained psychologists. By using trained buddies, the intervention costs will be very low. If proven effective, the intervention can be scaled up to different settings which could be an advantage for its cost-effectivity.

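### Training groups are randomised, but the named outcome models and the sample size make no allowance for clustering; the direction of the error is clear, its size is not

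*Protocol article*

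**What the plan says.** **Allocation.** Under Randomization and blinding, "participants will be randomly allocated to three conditions in a 1:1:2 allocation ratio using computer generated random numbers". The next sentence makes the training group the unit: "randomization will be done on group level", which the article explains as "potential participants attending a specific training session at a community center will be randomized to the same intervention arm". The reason given is the "low number of participants per group session"; no number is stated.

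**Delivery.** The intervention is also received in groups: "A core element of SM is its group-based format". The head-start stamp card is likewise assigned by group (Nudges).

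**Sample size.** Sample size calculations cites earlier studies that recommend 20 to 500 participants per condition "with an alpha error of 0.05 and a power of 0.80". It adds 10% attrition and arrives at 300. It gives no effect size, group size, number of groups, ICC or design effect, and names G*Power as the tool.

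**Analysis.** Data analysis uses t-tests, chi-square and Fisher's exact tests for the baseline description. Outcomes get logistic regression (two categories) or multinomial regression (more than two). On covariates: "Age, gender, and nationality will be treated as potential confounding variables". Group, trainer and centre are not mentioned.

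**Discussion.** Among the strengths: "Random allocation of study participants to the different conditions excludes all possible bias (selection and allocation bias". This describes allocation of individuals.

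**The concern.** Allocating whole groups makes this a cluster randomised trial. Members of a group share a neighbourhood centre, a trainer, each other's company and a stamp-card version, and some may have recruited one another, since snowball sampling is one of the recruitment routes. Their outcomes are likely to be correlated. Logistic and multinomial regression as named treat each participant as an independent observation, so their standard errors are too small when that correlation is positive. Covariates at the level of the person do not repair this.

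The error runs one way, towards false positive findings, and it touches every between-arm comparison. The authors intend the results to inform practice and possible scale-up, so a wrongly positive result would have consequences. The same omission in the sample size means that the trial has less power than the same number of individually randomised participants would give.

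Timing matters too. Data collection is ongoing, and if group membership is not recorded for control participants now, a valid analysis may not be possible later.

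**Working it through.** **1. The plan's own figure.** The total of 300 cannot be derived, because no effect size, SD or event rate is given. Only the attrition step can be checked: 300 × 0.90 = 270 evaluable, and 270 / 0.90 = 300.

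**2. A reference effect, by assumption.** If the 2 in 1:1:2 is the control arm (the text does not say, and the figure is not shown), the evaluable split is 135 in the two intervention arms pooled against 135 controls. At two-sided 0.05 and power 0.80 under independence, the detectable standardised difference is (1.960 + 0.842) × √(1/135 + 1/135) = 0.34. For one intervention arm against control (67.5 v 135) it is 0.42. These are back-solved values that only fix a starting point of 80%; the article states neither.

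**3. Formulas.** With group size m:
- design effect DE = 1 + (m − 1) × ICC
- actual two-sided error of the unadjusted test = 2 × [1 − Φ(1.96/√DE)]
- actual power = Φ(2.802/√DE − 1.96)
- effective sample size = 270/DE

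**4. Results.** Group sizes and ICCs are assumptions, with equal correlation in all arms.

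| m | ICC | DE | Type I error | Power | Effective N |
|---|---|---|---|---|---|
| 4 | 0.01 | 1.03 | 5.35% | 79% | 262 |
| 4 | 0.05 | 1.15 | 6.8% | 74% | 235 |
| 4 | 0.10 | 1.30 | 8.6% | 69% | 208 |
| 8 | 0.01 | 1.07 | 5.8% | 77% | 252 |
| 8 | 0.02 | 1.14 | 6.6% | 75% | 237 |
| 8 | 0.05 | 1.35 | 9.2% | 67% | 200 |
| 8 | 0.10 | 1.70 | 13.3% | 57.5% | 159 |

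Worked line (m = 8, ICC 0.05): DE = 1 + 7 × 0.05 = 1.35 and √1.35 = 1.162. Then 1.96/1.162 = 1.687, giving an error of 9.2%, and 2.802/1.162 − 1.96 = 0.45, giving power of 67%.

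**5. Check on the kind of model the plan names.** An unadjusted two-group logistic Wald test was simulated with beta-binomial groups, event probability 0.5 and 20,000 runs. With 16 groups of 8 per arm, it rejected in 5.2% of runs at ICC 0, 5.8% at 0.01, 7.0% at 0.02, 9.6% at 0.05 and 13.6% at 0.10, close to the formula. With 27 groups of 5 per arm, the figures were 4.2%, 4.8%, 5.5%, 6.7% and 9.2%. There the test is slightly conservative even without clustering, so the excess at ICC 0.01 shows against 4.2%, not against 5%.

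**6. If controls are uncorrelated.** With correlation in the intervention half only, the pooled design effect is the average of DE and 1, that is 1 + (m − 1) × ICC/2. Over the same range (m = 4 with ICC 0.01, to m = 8 with ICC 0.10) it is 1.015 to 1.35, with type I error of 5.2% to 9.2% and power of 79% to 67%.

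**The case against.** The strongest reply is that a journal article condenses the plan. Its analysis section gives model families with examples, and also leaves out the contrast, the timepoint and baseline adjustment. Silence about a group term is weak evidence that one was ruled out. That is fair as to intent: the article does not say that clustering will be ignored. It does, however, name its models and covariates, and these do not match the unit of randomisation stated a few sections earlier. It also reports a sample size with no allowance for that unit. This is a mismatch in what is stated, not merely a detail left for later.

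Four objections to the size of the problem stand.

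- **T-tests.** A reader might infer that they are planned for the outcomes. The article uses them only for baseline description; the point rests on the outcome regressions.
- **Groups of eight.** A reader might take these from the pilot. The pilot's eight participants were assigned to one or other intervention condition and are not shown to have met as a single group. Actual groups may be smaller.
- **A fall from 80% power.** A reader might take this as a measured loss. With no effect size stated, 80% cannot be reproduced even under independence, and the article ties the figure to what earlier studies recommend.
- **Control arm.** Controls attend no sessions during the control period, so their correlation may be weaker, although group-level allocation still applies.

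**Conclusion.** The point holds as a mismatch between the unit of allocation and both the named outcome models and the sample size. For any positive ICC, the unadjusted tests understate uncertainty and power is below what independent randomisation would give.

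The magnitude is conditional. For group sizes of 4 to 8 and ICCs of 0.01 to 0.10, all assumed, type I error is about 5.35% to 13% and power about 79% to 58% of the time for an effect that would have 80% under independence. At the low end the problem is slight; at the high end it is serious. Weak correlation among controls pulls the upper end of the error down to about 9%.

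The stronger claim, that the trial's error rate and power are known to fail by a large margin, is not supported, because the article gives no group size, ICC or effect size. The correction is still needed, since the method as stated is wrong for the design and inexpensive to put right.

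**What to change.** - Describe the trial as group (cluster) randomised wherever the design is stated.
- Record the group identifier for every participant in all three arms, including the group in which control participants were allocated.
- Analyse between-arm outcomes with a method that accounts for group: a mixed model, GEE or a cluster-level analysis would each serve. Use a small-sample correction, because 300 participants in groups of 4 to 8 give only about 75 to 38 groups (300/4 and 300/8) across three arms.
- Restate power using 1 + (m − 1) × ICC over an ICC range of 0.01 to 0.10, with the assumed effect size and group size stated.
- Correct the Discussion sentence so that it describes allocation by group and does not claim that all bias is excluded.

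The cost is some rewording, one more data field and a different model specification. Confidence intervals will be wider and the stated power less favourable. No extra participants are needed for this correction. It does not restore the lost power: holding 80% for the same effect would take 300 × DE participants, about 309 to 510 over the assumed range, so the authors should state plainly what effect 300 can detect.

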**Fig. 4 Fig4:**
[figure not shown]
Randomization of study participants. SM = stress management condition; SM-B = Stress management + buddy condition; CC = control condition

Given the nature of the intervention, it is not possible to blind participants or the research team involved in delivering the intervention (IB and WV) and data collection (SS, AS and research assistants). Therefore, to reduce the risk of bias and to ensure that data collection is conducted in accordance with the ethical guidelines, research assistants will receive a training in data collection. Further, AS will maintain regular contact (biweekly meetings) with the research team to ensure that study procedures conducted are consistent with sound research design.

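### Giving the group randomisation to a principal investigator who also recruits and collects data unblinded does not secure allocation concealment, and the claims of bias protection are unsupported

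*Protocol article*

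**What the plan says.** Under Randomization and blinding, the article allocates participants 1:1:2 with computer-generated random numbers, after eligibility has been checked and consent obtained. The unit is the group: "potential participants attending a specific training session at a community center will be randomized to the same intervention arm". On who does this, it says: "To minimize the risk of bias, randomization will be done by the principal investigator".

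The initials given there for the principal investigator appear in two other roles:

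- **Recruitment.** Under Recruitment of study population, "the research team (SS, AS, IB, WV and research assistants) will give presentations about the research study". The screening questionnaire is handed out at these sessions. An eligible person then "he/she signs the informed consent and returns it to the research team".
- **Data collection.** In the blinding text after Fig. 4, "it is not possible to blind participants or the research team involved in delivering the intervention", and the same sentence extends this to "data collection (SS, AS and research assistants".

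The Discussion then claims full protection: "Random allocation of study participants to the different conditions excludes all possible bias (selection and allocation bias").

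**The concern.** Allocation concealment means that whoever enrols people cannot know or influence the arm they will enter. The usual way to secure it is to separate the person who holds the sequence from the people who recruit. Here the article combines those roles in one person and offers the combination as the safeguard.

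Group allocation makes this more important. When a whole session shares an arm, one leaked or foreseen allocation affects everyone who joins that session afterwards. The recruitment routes include personal phone calls, key figures in the community and snowball sampling, so acquaintances of people already in a group may come forward later.

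At stake is comparability of the arms at baseline. If more motivated smokers, or people readier to work on stress and finances, were guided towards intervention sessions, the arms would differ before treatment began. Stress, cigarette consumption, financial health and general health are self-reported. Breath carbon monoxide and heart rate variability are measured objectively, but objective measurement does not correct for who was selected into an arm. The planned covariates (age, gender and nationality) would not capture motivation.

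**Working it through.** The article gives no figure to reproduce on this point. The check sets its statements side by side.

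1. **Who randomises?** The principal investigator (Randomization and blinding).
2. **Does that person recruit?** Yes, as a named member of the team presenting at orientation sessions, to which signed consent forms are returned (Recruitment of study population). The article does not say that this person assigns individuals to sessions.
3. **Does that person collect data unblinded?** Yes (blinding text after Fig. 4).
4. **What protects concealment?** Two things: the order of steps (eligibility, consent, then allocation) and computer-generated numbers.
5. **Is that order enough for a group draw?** For one person, consent before allocation suffices if nobody can foresee the draw. For a group, every member's consent must precede the group's single draw. The article states the order for participants and then makes the session the unit. It does not say that the roster is closed at the draw or what happens to someone who comes forward afterwards.
6. **Does the Discussion claim follow?** No. Randomisation guards against selection bias only if allocation is concealed until enrolment into the unit is complete, and the text does not establish this. An unblinded, group-allocated design cannot support a claim that all such bias is excluded.

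**Illustration of size.** These inputs are partly assumptions.

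- The article gives 300 participants and 10% attrition: 300 × 0.9 = 270.
- I assume the double share of 1:1:2 is the control arm. The text does not say so, and Fig. 4 is not shown. Both intervention arms pooled against control then gives 135 v 135.
- I assume no treatment effect, a two-sided 5% test on a standardised outcome, independent observations, and a prognostic difference d caused by selection. The document gives no value for d.

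SE = √(2/135) = 0.1217; shift z = d / SE; P(reject) = Φ(z − 1.96) + Φ(−z − 1.96).

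| d (SD) | z | P(reject) |
|---|---|---|
| 0.05 | 0.41 | about 7% |
| 0.10 | 0.82 | about 13% |
| 0.20 | 1.64 | about 38% |

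Allowing for clustering lowers these values. With an assumed design effect of 1.35 to 1.7 applied to the variance, the 0.10 SD row falls to about 10% to 11%. The assumed d determines the result, so the table shows only that small differences matter. It does not estimate bias in this trial.

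**The case against.** The strongest counter-argument is that allocation comes after eligibility and consent and uses computer-generated numbers. If each draw is made only once a group is complete, nobody can foresee its arm, whoever operates the computer. An article also commonly leaves the custody of the sequence, any blocking and the closing of rosters to the full protocol, and Figs 3 to 5 and Table 1 are not shown here.

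Much of this stands. A reader might infer that the arrangement removes allocation concealment. The document does not support that: it does not say that a list is visible in advance, that arms are known before rosters close, or that people join groups already allocated. Nor does it say that randomisation is unrestricted, so nothing can be concluded about imbalance in the number of groups per arm. The principal investigator's access to the stored data has no bearing on concealment.

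The objection does not rescue what the article states. It names the person, gives the reason and claims complete protection. The missing mechanics may be elsewhere, but a draw made by someone who also recruits is not independent, and calling it a bias safeguard is wrong whatever the full protocol adds.

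**Conclusion.** The point holds as a weakness in a stated arrangement and as two unsupported statements. A loss of concealment has not been demonstrated. Consent before allocation protects the individual's enrolment only if the group's roster is complete when its arm is drawn, and the article does not establish that. Concealment therefore depends on one person who also recruits and collects data.

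The size cannot be derived from the document. The range of about 7% to 38% rests on an assumed shift of 0.05 to 0.2 SD, an assumed 135 v 135 comparison and no clustering. The conclusion does not depend on it. The change is worth making because it is cheap and because the planned covariate adjustment could not be relied on to repair selective entry into groups.

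**What to change.** - Have the computer-generated 1:1:2 group-level sequence generated and held in a locked tool, or by an existing colleague with no recruiting or data-collection role.
- If blocks are used, vary their size and keep it concealed. In an openly unblinded group trial, fixed blocks would make later allocations predictable.
- Release a group's arm only after its roster is closed, all consents are signed and T0 is complete. Send later arrivals to the next unallocated group.
- Under Randomization and blinding, replace the bias rationale with a description of this procedure. In the Discussion, withdraw the claim that all selection and allocation bias is excluded.
- For groups already allocated, report when each roster closed relative to the allocation.

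The change is procedural and needs no new staff. It costs a short wait between T0 and the first session, and late arrivals wait for the next group.
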